**FAV1**

**FAV2**

**FAV3**

**FAV4**

**FAV5**

**FAV6**

**FAV7**

**FAV8**

**FAV9**

**FAV10**

**FAV11**

**FAV12**

**FAV13**

**FAV14**

**FAV15**

**FAV16**

| Pepper | | Small finger size |  | 1 | 2 | 3 | 4 | 5 |
| --- | --- | --- | --- | --- | --- | --- | --- | --- |
| Tomatoes | | Empty milk tin size |  | 1 | 2 | 3 | 4 | 5 |
| **19. Tubers** | | **Handy measure** | **Number** | **(1) Never** | **(2) 2-3** | **(3) 4-5** | **(4) 6 Times** | **(5) Daily** |
| **and Plantain** | |  | **consumed** |  | **Times** | **Times** | **per week** |  |
|  | |  |  |  | **per week** | **per week** |  |  |
| Cassava | | Empty sardine tin size |  | 1 | 2 | 3 | 4 | 5 |
| Plantain | | Medium size |  | 1 | 2 | 3 | 4 | 5 |
| Cocoyam | | Standard egg size |  | 1 | 2 | 3 | 4 | 5 |
| Sweet potato | | Standard egg size |  | 1 | 2 | 3 | 4 | 5 |
| White potato | | Standard egg size |  | 1 | 2 | 3 | 4 | 5 |
| Yam | | Empty sardine tin size |  | 1 | 2 | 3 | 4 | 5 |
| **20. Cereals** | | **Handy measure** | **Number** | **(1) Never** | **(2) 2-3** | **(3) 4-5** | **(4) 6 Times** | **(5) Daily** |
| **& Grains** | |  | **consumed** |  | **Times** | **Times** | **per week** |  |
|  | |  |  |  | **per week** | **per week** |  |  |
| Maize | | Empty milk tin size |  | 1 | 2 | 3 | 4 | 5 |
| Millet | | Empty milk tin size |  | 1 | 2 | 3 | 4 | 5 |
| Oats | | Soup spoon/ladle |  | 1 | 2 | 3 | 4 | 5 |
| Rice (white) | | Soup spoon/ladle |  | 1 | 2 | 3 | 4 | 5 |
| Rice (brown) | | Soup spoon/ladle |  | 1 | 2 | 3 | 4 | 5 |
| Sorghum |  | Soup spoon/ladle |  | 1 | 2 | 3 | 4 | 5 |
| (similar | to |  |  |  |  |  |  |  |
| corn) |  |  |  |  |  |  |  |  |
| Wheat | | Soup spoon/ladle |  | 1 | 2 | 3 | 4 | 5 |
| **21. Legumes** | | **Handy measure** | **Number** | **(1) Never** | **(2) 2-3** | **(3) 4-5** | **(4) 6 Times** | **(5) Daily** |
|  |  |  | **consumed** |  | **Times** | **Times** | **per week** |  |
|  |  |  |  |  | **per week** | **per week** |  |  |
| Agushie | | Stewing spoon level |  | 1 | 2 | 3 | 4 | 5 |

**FAV17**

**TUP1**

**TUP2**

**TUP3**

**TUP4**

**TUP5**

**TUP6**

**CEG1**

**CEG2**

**CEG3**

**CEG4**

**CEG5**

**CEG6**

**CEG7**

**LEG1**

**LEG2**

| Bambara | | Stewing spoon level |  | 1 | 2 | 3 | 4 | 5 |
| --- | --- | --- | --- | --- | --- | --- | --- | --- |
| beans | |  |  |  |  |  |  |  |
| Cowpea | | Stewing spoon level |  | 1 | 2 | 3 | 4 | 5 |
| Groundnut | | Stewing spoon level |  | 1 | 2 | 3 | 4 | 5 |
| Palm nut | | Empty milk tin size |  | 1 | 2 | 3 | 4 | 5 |
| Soyabeans |  | Stewing spoon level |  | 1 | 2 | 3 | 4 | 5 |
| (similar | to |  |  |  |  |  |  |  |
| and used | as |  |  |  |  |  |  |  |
| substitute | to |  |  |  |  |  |  |  |
| corn) |  |  |  |  |  |  |  |  |
| Tiger nuts | | Stewing spoon level |  | 1 | 2 | 3 | 4 | 5 |
| **22. Animal** | | **Handy measure** | **Number** | **(1) Never** | **(2) 2-3** | **(3) 4-5** | **(4) 6 Times** | **(5) Daily** |
| **Products** | |  | **consumed** |  | **Times** | **Times** | **per week** |  |
|  | |  |  |  | **per week** | **per week** |  |  |
| Eggs | | Egg size |  | 1 | 2 | 3 | 4 | 5 |
| Fish | | Empty sardine tin size |  | 1 | 2 | 3 | 4 | 5 |
| Milk | | Small tin size |  | 1 | 2 | 3 | 4 | 5 |
| Milk powder | | Tablespoon level |  | 1 | 2 | 3 | 4 | 5 |
| Chicken | | Match box size |  | 1 | 2 | 3 | 4 | 5 |
| Red | | Standard egg size |  | 1 | 2 | 3 | 4 | 5 |
| meat/Beef | |  |  |  |  |  |  |  |
| Salted fish | | Match box size |  | 1 | 2 | 3 | 4 | 5 |
| (such as | |  |  |  |  |  |  |  |
| **koobi**-salted | |  |  |  |  |  |  |  |
| tilapia, | |  |  |  |  |  |  |  |
| **momoni**,- | |  |  |  |  |  |  |  |
| salted fish | |  |  |  |  |  |  |  |
| left to | |  |  |  |  |  |  |  |

**LEG3**

**LEG4**

**LEG5**

**LEG6**

**LEG7**

**ANP1**

**ANP2**

**ANP3**

**ANP4**

**ANP5**

**ANP6**

**ANP7**

**ANP8**

**ANP9**

**FAL1**

**FAL2**

**FAL3**

**FAL4**

**FAL5**

**FAL6**

**FAL7**

**FAL8**

**SDS1**

**SDS2**

| ferment, | | |  |  |  |  |  |  |  |
| --- | --- | --- | --- | --- | --- | --- | --- | --- | --- |
| **kako**-salted | | |  |  |  |  |  |  |  |
| herring) | | |  |  |  |  |  |  |  |
| Seafood | |  | Small finger size |  | 1 | 2 | 3 | 4 | 5 |
| (such |  | as |  |  |  |  |  |  |  |
| shrimp, |  |  |  |  |  |  |  |  |  |
| lobster, | etc) |  |  |  |  |  |  |  |  |
| Snail | | | Small tomato tin size |  | 1 | 2 | 3 | 4 | 5 |
| **23. Fats and** | | | **Handy measure** | **Number** | **(1) Never** | **(2) 2-3** | **(3) 4-5** | **(4) 6 Times** | **(5) Daily** |
| **oils** | | |  | **consumed** |  | **Times** | **Times** | **per week** |  |
|  | | |  |  |  | **per week** | **per week** |  |  |
| Coconut oil | | | Stewing spoon level |  | 1 | 2 | 3 | 4 | 5 |
| Groundnut | | | Stewing spoon level |  | 1 | 2 | 3 | 4 | 5 |
| oil | | |  |  |  |  |  |  |  |
| margarine | | | Stewing spoon level |  | 1 | 2 | 3 | 4 | 5 |
| Palm | kernel | | Stewing spoon level |  | 1 | 2 | 3 | 4 | 5 |
| oil |  |  |  |  |  |  |  |  |  |
| Palm oil | | | Stewing spoon level |  | 1 | 2 | 3 | 4 | 5 |
| Refined | | | Stewing spoon level |  | 1 | 2 | 3 | 4 | 5 |
| vegetable oil | | |  |  |  |  |  |  |  |
| Sheabutter | | | Stewing spoon level |  | 1 | 2 | 3 | 4 | 5 |
| oil | | |  |  |  |  |  |  |  |
| Soya oil | | | Stewing spoon level |  | 1 | 2 | 3 | 4 | 5 |
| **24.** | **Soft** | | **Handy measure** | **Number** | **(1) Never** | **(2) 2-3** | **(3) 4-5** | **(4) 6 Times** | **(5) Daily** |
| **Drinks** |  | **&** |  | **consumed** |  | **Times** | **Times** | **per week** |  |
| **Sweets** |  |  |  |  |  | **per week** | **per week** |  |  |
| Chocolate | | | 1 segment size |  | 1 | 2 | 3 | 4 | 5 |
| Energy drink | | | 350 mls pack size |  | 1 | 2 | 3 | 4 | 5 |

**SDS3**

| Fruit juice | 250 mls pack size | |  | 1 | 2 | 3 | 4 | | 5 |
| --- | --- | --- | --- | --- | --- | --- | --- | --- | --- |
| Malt drink | 330 mls bottle size | |  | 1 | 2 | 3 | 4 | | 5 |
| Minerals | 300 mls bottle size | |  | 1 | 2 | 3 | 4 | | 5 |
| (coke, fanta, |  |  |  |  |  |  |  |  |  |
| sprite, etc) |  |  |  |  |  |  |  |  |  |
| Toffees | 1 average toffee size | |  | 1 | 2 | 3 | 4 | | 5 |
| Sugar (you | Teaspoon size | |  | 1 | 2 | 3 | 4 | | 5 |
| add to food) |  |  |  |  |  |  |  |  |  |
| **25. Snacks** | **Handy measure** | | **Number** | **(1) Never** | **(2) 2-3** | **(3) 4-5** | **(4) 6 Times** | | **(5) Daily** |
|  |  |  | **consumed** |  | **Times** | **Times** | **per week** | |  |
|  |  |  |  |  | **per week** | **per week** |  | |  |
| Biscuit | **1 biscuit** | **(cream** |  | **1** | **2** | **3** | **4** | | **5** |
|  | **crackers size)** |  |  |  |  |  |  |  |  |
| Cakes | Orange size | |  | 1 | 2 | 3 | 4 | | 5 |
| Chips | Empty sardine tin size | |  | 1 | 2 | 3 | 4 | | 5 |
| Doughnuts | Large egg size | |  | 1 | 2 | 3 | 4 | | 5 |
| Fried chicken | Match box size | |  | 1 | 2 | 3 | 4 | | 5 |
| Fried egg | Standard egg size | |  | 1 | 2 | 3 | 4 | | 5 |
| Ice cream | Empty small tomato tin  size | |  | 1 | 2 | 3 | 4 | | 5 |
| Meat/sausage | Empty small tomato tin  size | |  | 1 | 2 | 3 | 4 | | 5 |
| khebab |  |  |  |  |  |  |  |  |  |
| Popcorn | Empty milk tin size | |  | 1 | 2 | 3 | 4 | | 5 |
|  |  |  |  |  |  |  |  |  |  |
| **26. Water** | **Handy measure** | | **Number** | **(1)** | **(2) 1 per** | **(3) 2-3** | **(4)** | **4-5** | **(5) 6 or** |
| **consumption** |  |  | **consumed** | **Rarely** | **day** | **Times** | **Times** | **per** | **more times** |
|  |  |  |  |  |  | **per day** | **day** |  | **per day** |
| Water (daily) | 500 mls (sachet water) | |  | 1 | 2 | 3 | 4 | | 5 |

**SDS4**

**SDS5**

**SDS6**

**SDS7**

**SKS1**

**SKS2**

**SKS3**

**SKS4**

**SKS5**

**SKS6**

**SKS7**

**SKS8**

**SKS9**

**WATER**

**27. How often do you normally add salt to your already prepared/cooked meal? SALTINT**

| 1. Never | 2. Rarely | 3. Occasionally | 4. Very often |
| --- | --- | --- | --- |

**28. Please circle the one you prefer to eat at any time. Circle one response per row**

| 1. Banana | **Or** | 2. Biscuit |
| --- | --- | --- |
| 1. Ice cream | **Or** | 2. Orange |
| 1. Watermelon | **Or** | 2. Soft drink |
| 1. Baked chicken | **Or** | 2. Fried chicken |
| 1. White bread | **Or** | 2. Wheat bread |
| 1. Chips | **Or** | 2. Corn |

**BANBS ICEOR**

**WATSOF**

**BAKED WHITEB CHIPCON**

**29. Circle the one you think is good for your health. Circle one response per row**

| 1. Banana | **Or** | 2. Biscuit |
| --- | --- | --- |
| 1. Ice cream | **Or** | 2. Orange |
| 1. Watermelon | **Or** | 2. Soft drink |
| 1. Baked chicken | **Or** | 2. Fried chicken |
| 1. White bread | **Or** | 2. Wheat bread |
| 1. Chips | **Or** | 2. Corn |

**BANBS2**

**ICEOR2**

**WATSOF2**

**BAKED2**

**WHITEB2**

**CHIPCON**

**SECTIONS 3 AND 4**

**SMOKING AND ALCOHOL**

We want to find out your knowledge, attitude and behavior relating to lifestyle and health on smoking and alcohol. Please do not write your name on the questionnaire. Confidentiality is assured. Please answer honestly to all questions as they appear. This is not a test, there are no right or wrong answers.

**SECTION 3: SMOKING**

**The following questions ask about your use of tobacco.**

**30. Have you ever tried cigarette smoking, even one or two puffs? TRIEDSMO**

1. Yes 2. No

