**3.11 Intervention**

At this stage permissions and consent would had been sought from the Ministry of Education, District Directors of Education, Chairmen of the Parent Teacher Associations, parents/guardians, and students to carry out the study. All materials for the study will be ready at this stage. The objectives of the study and the eligibility criteria to participate in this study will be explained to all the students’ involved. Students will go through medical check-up which will be carried out by the two clinicians in order to pass eligibility criteria to be enrolled into the study.

The self-administered questionnaire will be given to students to complete. Health staff will measure students anthropometric and blood pressure measurements. Confidentiality and anonymity will be assured at all stages of the study. The module will be implemented in the intervention schools for a period of six months but not in the control schools. Then at the end of six months the same questionnaire will be given to students in both the intervention and the control schools. Health staff who will not take part during the baseline data collection will take anthropometric and blood pressure measurements of students at post intervention study. A total of 848 students will participate in the study; intervention (424) and the control (424) schools. Contamination of the intervention will be prevented by having intervention and control schools with distances between them.

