**3.12.2 Questionnaire**

The questionnaire will be pre-tested and assisted self-administered questionnaire in English language as in Appendix. The questionnaire will be divided into ten sections namely, socio demography, dietary intake, smoking, alcohol consumption, physical activity, CVD knowledge, motivation, behavioral skills, BMI (weight and height), and blood pressure (diastolic and systolic). The questionnaires will be administered in a classroom setting in all the selected schools.

Section one of the questionnaire will be used to access students’ age, gender, grade, ethnicity, monthly pocket money, and family history. Data on age will be collected in the form of open ended question and students will fill in the blank space provided. The rest (ethnicity, gender, religion, and family history) are in the form of closed ended questions and students are to choose the answers that will pertained to them.

Section two is a seven-day dietary recall instrument which are foods items mostly consumed in Ghana, the Ghana Demographic and Health Survey, (GDHS), (GSS, 2009; Nti, 2008) to assess dietary consumption. Amounts of each food intake will be stated with the use of handy measure tables (food weights). This are based on the weights of foods with their equivalent handy measure tables which are commonly used

in Ghana (Owusu, Ankrah, Boateng, & Anteh, 1995). Then frequency of consumption of certain foods will be scored based on one (1) for never dietary consumption, two (2) for 2-3 times per week, three (3) for 4-5 times per week, four (4) for 6 times per week, and five (5) for daily intake of a particular food item.

Section three and four are the modified smoking and alcohol questionnaires, Global Youth Tobacco Survey (GYTS) developed by WHO and Centre for Disease Control and Prevention (CDC) (CDC, 2008). It is a school-based adolescents’ self- administered questionnaire which comprised of a set of core questions that will be used to evaluate tobacco and alcohol control and prevention programmes among secondary school students. Students would be classified as never, ever, and current smokers and alcohol consumption. Strict confidentiality will be ensured among researchers to avoid disclosure of smoking and alcohol statuses to school authorities, teachers, or parents.

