**3.16.4 Smoking**

Smoking will be categorized into ex-smokers, current smokers, and never smoker. Ever smokers were students who had ever tried smoking before but had stopped. Current smokers are those who are currently smoking tobacco. Never-smokers referred to as students who has never smoked tobacco.

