**3.17.3 Inferential Statistics**

Chi-square tests will be performed to compare baseline characteristics of groups by their socio-demographic factors, family factors, CVD knowledge, motivation, behavioral skills, physical activity, smoking status, alcohol intake, BMI, systolic and diastolic BP. Independent t-tests will be performed to determine the between groups differences of total knowledge, motivation, behavioral skills, physical activities, dietary intake, BMI, diastolic and systolic BP. At six months post intervention, the independent and paired sample t-tests would be performed to determine the between and within group differences of variables respectively. Chi-square and the McNemar tests will also be performed on smoking status and alcohol intake at six months to determine the difference between and within groups since the variables are categorical variables.

A mixed design repeated measures analysis of variance (ANOVA) will be performed after checking that there is no substantial non-normality of residuals to determine the between and within group differences and its interactions on time differences on CVD knowledge, motivation, behavioral skills, physical activity, dietary intake, body weight, BMI, diastolic and systolic BP. Intention-to- treat (ITT) analysis will be the method that will be used to handle missing data in the analysis. Replacement of data will then be conducted for each missing variable using the multiple imputation method, following which Generalized Linear Mixed Model (GLMM) analysis will be performed to determine the overall effectiveness of the intervention study.

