**31. Do you still smoke?** 1. Yes 2. No **STILLSMO**

**32. How old were you when you first tried a cigarette?**

3. NA **AGESMO**

**33. During the past 30 days (one month) on, how many days did you smoke cigarettes?**

**DAYSM**

99. NA Circle 99 if not applicable

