**48. Have you ever taken alcohol before?**

1. Yes 2. No **EVERALCO**

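### The lifetime smoking and alcohol questions are repeated at six months with no rule for a student who takes back an earlier yes, so a never/ever comparison can show a fall in use that did not happen

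*Protocol*

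**What the plan says.** Section 3.11 repeats the form: "Then at the end of six months the same questionnaire will be given to students in both the intervention and the control schools". Appendix A contains two lifetime items with no recall window: item 30, "Have you ever tried cigarette smoking, even one or two puffs", and item 48, "Have you ever taken alcohol before". Current use is asked separately, for smoking in item 31 ("Do you still smoke") and for alcohol in item 49. Age at first use is asked in item 32 ("How old were you when you first tried a cigarette") and item 51.

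Section 3.12.2 sets the categories: "Students would be classified as never, ever, and current smokers and alcohol consumption". Section 3.16.4 defines the smoking groups. An ever (ex-) smoker has tried and stopped, and for the third group it says "Never-smokers referred to as students who has never smoked tobacco". Section 3.16.5 says which drinks count as alcohol but defines no user categories.

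Section 3.17.3 fixes the tests: "Chi-square and the McNemar tests will also be performed on smoking status and alcohol intake at six months", the first between and the second within groups. Hypotheses 4 and 5 in section 1.6 speak of reducing prevalence, between groups and within groups from baseline, without saying whether ever-use or current use is meant. Smoking and alcohol are both primary outcomes (section 3.15.2).

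**The concern.** Having tried a cigarette or a drink cannot be undone. A truthful yes at baseline cannot become a truthful no six months later. Yet the protocol asks the question twice, builds the category from it, and never says that the earlier answer limits the later one. If six-month status is taken from the six-month form, a student who retracts is recorded as having moved from ever-use to never-use. A test on a split that separates never from ever would count that as improvement.

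The intervention schools are visited three times a week for six months with teaching that includes the harms of smoking and alcohol (section 3.14 and Table 3.4). The students then report on themselves in a classroom. It is reasonable to fear more retraction there than in control schools. Two primary outcomes depend on these answers.

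**Working it through.** **Tracing the rule.** Take a student who answers yes to item 30 at baseline and no at six months. Section 3.12.2 and the six-month answer give never-smoker. Section 3.16.4 reserves that label for someone who has never smoked, which the baseline answer contradicts. Nothing in sections 3.12, 3.16 or 3.17 says which answer prevails. For alcohol the same conflict follows from the wording of item 48 and the categories in 3.12.2.

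**Which analyses are exposed.**
- Never v ever, or three-level status: exposed.
- Current use (items 31 and 49): a retracting ex-user is a non-user at both waves, so nothing changes.
- Initiation among students who said no at baseline: students with a baseline yes are outside the denominator, so retraction has no effect.

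McNemar's test in its usual form needs two categories, and the protocol does not say where the three-level status is cut.

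**Inputs for an illustration.** The protocol gives no retraction rate, so there is no figure of its own to reproduce.
- From the protocol: 424 students per arm (section 3.11); alcohol use 42.3% (section 1.1); current alcohol use 12.6% (section 2.6.3.2); smoking 2.4% in boys and 1.4% in girls (section 1.1), taken as 2%.
- Assumed: these prevalences stand for ever-use; true initiation is 2% in both arms; retraction is 5% in control and 15%, 20% or 25% in intervention; there is no true effect, clustering or dropout; the split is never v ever.

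**Between groups.** Expected ever-use at six months is p(1 − r) + 0.02(1 − p). For p = 0.423:
- Control: 0.423 × 0.95 + 0.02 × 0.577 = 0.4134.
- Intervention, r = 0.15: 0.423 × 0.85 + 0.02 × 0.577 = 0.3711.
- Gap d = 0.423 × (0.15 − 0.05) = 0.0423.

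Rejection probability ≈ Φ((d − 1.96·s0)/s1). With mean proportion 0.392, s0 = √(2 × 0.392 × 0.608/424) = 0.0335, and s1 is also 0.0335. This gives Φ((0.0423 − 0.0657)/0.0335) = Φ(−0.70) ≈ 0.24. A simulation of 40,000 trials per row agrees with this approximation and supplies the McNemar and carry-forward columns.

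| Ever-use | Retraction, control v intervention | Gap, points | Chi-square rejects | McNemar shows a fall, intervention arm | Chi-square with baseline yes carried forward |
|---|---|---|---|---|---|
| 42.3% | 5% v 15% | 4.2 | 24% | 98% | 5% |
| 42.3% | 5% v 20% | 6.3 | 48% | over 99% | 5% |
| 42.3% | 5% v 25% | 8.5 | 72% | over 99% | 5% |
| 12.6% | 5% v 15% | 1.3 | 9% | 2% | 5% |
| 12.6% | 5% v 20% | 1.9 | 13% | 8% | 5% |
| 12.6% | 5% v 25% | 2.5 | 20% | 19% | 5% |
| 2% | 5% v 25% | 0.4 | 6% | under 1% | 5% |

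Equal retraction in both arms (5% v 5%) leaves the chi-square test at about 5%.

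**Within one group.** Here no difference between arms is needed. With 424 × 0.423 ≈ 179 ever-drinkers and no initiators, 5% retraction gives 9 false moves and an exact McNemar p of 2 × 0.5⁹ = 0.004. At 12.6% (53 ever-drinkers), 10% retraction gives 5 moves, p = 0.06, and 20% gives 11, p = 0.001. At 2% (8 smokers), even 30% retraction gives about 3 moves at most, p = 0.25. True initiators offset these moves: with 2% initiation, 5% retraction at 42.3% gives a significant false fall in about 12% of trials.

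**The case against.** The strongest reply is that silence is not a rule. No sentence says each wave is classified alone. Data are to be checked and cleaned (section 3.17), code numbers allow the waves to be linked (section 3.18), and consistency rules often sit in an analysis or data-management plan that is not shown. The definition of a never-smoker, read strictly, already excludes a student with a baseline yes. This stands as a limit on the wording: classification by single wave is the literal reading, not a stated one. It does not remove the point, because the protocol itself defines the categories and names the tests, and those definitions are incomplete for two waves.

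A reader might infer that every retraction counts as a programme success. That needs a never/ever or three-level split, which the protocol does not fix. A current user who retracts does count favourably, but would do so equally by answering no to item 31.

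A reader might also infer that any fall in ever-use must be misreporting. That goes too far. Section 3.16.4 uses ever for tried and stopped, so relapse lowers that category truthfully. Loss of ever-users to follow-up can also lower the proportion, and section 3.6 plans for 20% attrition.

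The 5% reference is that of a test without clustering. With 848/4 = 212 students per school and the protocol's ICC of 0.01, the design effect is 1 + 211 × 0.01 = 3.11. An unadjusted chi-square test would then reject in about 2(1 − Φ(1.96/√3.11)) = 27% of null trials with no retraction at all. The illustration isolates retraction and is not a forecast of the trial's error rate. It also does not evaluate the mixed model that section 3.17.3 assigns to overall effectiveness.

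**Conclusion.** The concern holds as a gap in the outcome definition. The protocol repeats two lifetime questions, classifies and tests status, and gives no rule for a retracted yes, so an impossible move can be read as a reduction in use.

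Its size depends on choices and rates the documents do not give. For alcohol at 42.3%, with the split and retraction rates assumed above, false between-group rejection is about 24% to 72%; at 12.6% it is about 9% to 20%. Treating either prevalence as ever-use is an assumption, and the 12.6% is stated as current use. For smoking at about 2% the effect is negligible. That prevalence may understate how many have tried one or two puffs, but the protocol offers no higher figure for ever-trying.

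The documents do not support the stronger conclusion that both primary outcomes are biased towards the programme. Equal retraction gives no between-group bias, and greater retraction in intervention schools is plausible, not shown. Current use, and initiation among students who said no at baseline, are unaffected by retraction of ex-use.

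**What to change.** In sections 3.16.4 and 3.16.5, state that a baseline yes on item 30 or 48 is carried forward, so that the student can only be an ex-user or a current user at six months. In section 3.17.3, name current use (items 31 and 49) as the variable tested for the prevalence hypotheses, and test new use only among students who said no at baseline. Report the number of contradictory answers by arm.

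Use items 32 and 51 only descriptively or in a sensitivity analysis. Age in whole years is too coarse to date first use: a student who first tried at the same age, up to nearly a year before baseline, would pass as a new user.

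The cost is a few sentences and a few lines of derivation, with no new data. Two limits remain. A false yes at baseline is kept, but it precedes allocation, so the intervention cannot have caused it. Denial of current use at item 31 or 49 is not corrected.
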